## Secondary outcomes

Secondary outcome measures are:

1. Mortality (all cause), measured in days from randomisation until first event or until the end of the trial (minimum 2 years) where no event occurs
2. Cardiovascular events (myocardial infarction, stroke, admission for heart failure), measured in days from randomisation until first event or until the end of the trial (minimum 2 years) where no event occurs
3. Number of hospital admissions (including reasons for readmissions), following discharge from index surgical admission for up to 4.5 years
4. Number of re-interventions (including nature of re-intervention), following index surgical procedure for up to 4.5 years
5. All lower limb amputations (minor and major i.e. below and above ankle joint) measured in days from randomisation until first event or until the end of the trial (minimum 2 years) where no event occurs
6. Concomitant medications (specifically: use of statin, use of antithrombotic medication)
7. Estimated glomerular filtration rate (renal function) based on serum creatinine levels using the Chronic Kidney Disease Epidemiology (CKD-EPI) formula measured at 6 and 12 months and annually thereafter
8. Low Density Lipoprotein measured at 6 months
9. HbA1C measured at 6 months
10. Cholesterol measured at 6 months
11. Ankle Brachial Pressure Index (ABPI) measured at 6 and 12 months and annually thereafter
12. Types of endovascular devices used and/or name of surgery performed (open)
13. Quality-of-life using the EQ-5D-5L measured at 6 and 12 months and annually thereafter
14. Healthcare resource use and costs measured across follow-up assessments over a minimum of 24 months and until the end of the trial

A prospectively planned economic evaluation will be conducted from an NHS and personal social services perspective as per NICE recommendations.

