## Trial assessments

### Baseline Visit (Day 0)

Once a Participant ID Number is allocated, the Baseline visit can take place. During this visit, participants will complete participant questionnaires, undergo a review of their medical history (including previous surgical interventions), cardiovascular risk factors, PAD anatomy, eGFR, HbA1C, LDL and cholesterol levels. If a female is thought to be pregnant, a urine pregnancy test will be performed as part of usual care ahead of surgery. Where a female participant is found to be pregnant, progression to treatment will be assessed using a risk-based approach as managed routinely by the patient’s treating clinician. Baseline visit biochemistry assessments/bloods to be taken in line with clinical pathway and matching the research schedule as closely as possible. It is understood that because these bloods are clinical, that there may be occasions where these bloods are taken ahead of the research baseline timepoint. Please refer to **Table 2** for further details about the Baseline visit, follow up visits and assessments.

### Review of Clinical Events – Day of Discharge, Day 30 and Months 6, 12, 24, 36, 48 and 54

A review of clinical events, particularly those related to the cardiovascular system, will be undertaken at the above trial visits including re-intervention, admission to hospital, death, myocardial infarction, stroke and new heart failure leading to admission. For visits at day 30, months 12, 36, 48 and 54, data collection will be performed either by telephoning the participant or retrieving the information from their medical notes. For visit month 6, the participant needs to attend clinic in person. However, if the participant cannot attend in person, as this is a pragmatic study this information can instead be collected remotely via telephone or through acquiring information through participant medical records.

### Biochemistry Assessments – Baseline and Month 6

Standard blood sample assessments to be undertaken in clinic at Baseline and month 6 and should include eGFR, total cholesterol, LDL cholesterol and HbA1C - these are NHS standard of care and constitute part of these patients regular care as per NHS and National Institute for Health and Care Excellence guidance. The blood samples (5ml collected at each visit) will be collected at room temperature before being processed and analysed at the local pathology laboratories as per each site’s standard procedures for these patients.

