### Ankle Brachial Pressure Index (ABPI) – Baseline and Months 6, 12, 24, 36, 48, 54

ABPI is a reliable way to detect arterial insufficiency and is the ratio of the ankle systolic blood pressure to the brachial systolic blood pressure. It will be measured using a sphygmomanometer and a hand-held Doppler device by appropriately trained personnel e.g., a research nurse or a clinician. This constitutes part of these patients regular care as per NHS and National Institute for Health and Care Excellence guidance.

An ABPI ratio of:

- < 0.5 suggests severe arterial disease
- > 0.5 to < 0.8 suggests the presence of arterial disease or mixed arterial/venous disease
- Between 08 – 1.3 suggests no evidence of significant arterial disease
- > 1.3 may suggest the presence of arterial calcification

Measurements at 30 days and months 6, 12, 36, 48 and 54 can be taken from the participant’s medical records.

### EuroQOL 5D 5L Questionnaire – Baseline and Months 6 and 12

EuroQOL- 5D (EQ-5D-5L) is a standardised assessment of health status to provide a simple, generic

measure of health for clinical evaluation (10, 11). It consists of 2 pages covering 5 dimensions (mobility, self-care, usual activities, pain/discomfort and anxiety/depression) and the participant is

asked to choose an accompanying statement which best describes how much ease or difficulty they

have in each of these dimensions (1 is scored as no problems/pain/anxiety/depression, 5 is scored as

unable to/extreme anxiety/depression). The questionnaire also asks the participant to indicate on a scale of 1-100 1 = the worst health you can imagine, 100 = the best health you can imagine how their health is on that day.

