**Table 2. Schedule of Assessments**

| **VISIT** | **Time points** | | | | | | | | | |
| --- | --- | --- | --- | --- | --- | --- | --- | --- | --- | --- |
|  | **Baseline** | **Trial intervention** | **Day of Discharge** | **30 Days** | **6 months** | **12 months** | **24 months** | **36 months^1^** | **48 months^1^** | **54 months^1^** |
| **Visit window (days)**  (± number of days this visit can take place ahead or after its due date) | - | **-** | **-** | ± 7 days | ± 30days | ± 30 days | ± 30 days | ± 30 days | ± 30 days | ± 30 days |
| **Day** | 0 |  |  | 30 | 180 | 365 | 730 | 1095 | 1460 | 1643 |
| Eligibility check | x |  |  |  |  |  |  |  |  |  |
| Obtain informed consent | x |  |  |  |  |  |  |  |  |  |
| Randomisation (allocation of treatment) | x |  |  |  |  |  |  |  |  |  |
| Demographics | x |  |  |  |  |  |  |  |  |  |
| Medical history including cardiovascular risk factors | x |  |  |  | x |  |  |  |  |  |
| Details of anatomy (arteries) | x |  |  |  |  |  |  |  |  |  |
| Concomitant medications (statins and antithrombotics) | x |  | x | x | x | x | x | x | x | x |
| Review of clinical events |  |  | x | x | x | x | x | x | x | x |
| Days lost from regular activities |  |  |  |  | x | x | x | x | x | x |
| Estimated Glomerular Filtration Rate (eGFR) | x |  |  |  | x |  |  |  |  |  |
| Low Density Lipoprotein (LDL) value | x |  |  |  | x |  |  |  |  |  |
| Total Cholesterol value | x |  |  |  | x |  |  |  |  |  |
| HbA1C value | x |  |  |  | x |  |  |  |  |  |
| Ankle Brachial Pressure Index (ABPI) | x |  |  |  | x | x | x | x | x | x |
| EQ-5D-5L questionnaire | x |  |  |  | x | x | x | x | x | x |
| Details of intervention (type of surgery or endovascular treatment configuration and devices) |  | x |  |  |  |  |  |  |  |  |
| Admission to hospital or visit to primary care |  |  |  |  | x | x | x | x | x | x |
| Assessment of Adverse Events | x | x | x | x | x | x | x | x | x | x |

^1^ The follow up trial visitsmay be undertaken remotely either via telephone or through acquiring information through participant medical records. For 6 months, in the first instance please try to bring the patient in for a face-to-face appointment. If this is not possible then this follow-up visit may also be undertaken remotely via telephone or through acquiring information through participant medical records.

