## Follow-up

The minimum follow up period for participants is 24 months after the time of randomisation. All follow up data will be collected from the date of randomisation. For month 6 follow-up, please make all efforts to ensure this takes place in person at the vascular clinic (as part of standard of NHS care appointments post-operatively). From month 12 onwards follow-up can be conducted via telephone or through collecting data from participant medical records. Please refer to **Table 2** for further details about follow up visits.

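### The protocol gives conflicting measurement times for eGFR and EQ-5D-5L, and it allows records-only visits without saying how the EQ-5D-5L is then obtained.

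*Protocol*

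**What the plan says.** **eGFR.** Section 4.2, item 7, specifies the "Chronic Kidney Disease Epidemiology (CKD-EPI) formula measured at 6 and 12 months and annually thereafter". The heading of section 8.4.3 reads "Biochemistry Assessments – Baseline and Month 6", and its text says "Standard blood sample assessments to be undertaken in clinic at Baseline and month 6 and should include eGFR". The eGFR row of Table 2 is marked at baseline and 6 months and nowhere else.

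**EQ-5D-5L.** Section 4.2, item 13, lists "Quality-of-life using the EQ-5D-5L measured at 6 and 12 months and annually thereafter". Table 2 marks the questionnaire at baseline and at 6, 12, 24, 36, 48 and 54 months. The heading of section 8.4.5 is "EuroQOL 5D 5L Questionnaire – Baseline and Months 6 and 12". The text under it describes the instrument and gives no schedule of its own.

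**Mode of follow-up.** Section 8.5 states: "From month 12 onwards follow-up can be conducted via telephone or through collecting data from participant medical records". Section 8.4.2 and the Table 2 footnote extend the same latitude to month 6 when the participant cannot attend in person.

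**Use of the data.** Cost-effectiveness is part of the primary objective (section 3.2). Section 11.6.5 derives utilities from the EQ-5D-5L and proposes to examine missing data, with multiple imputation as an example. Section 11.6 analyses secondary outcomes on complete cases.

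**The concern.** An outcome definition and a visit schedule have to name the same time points, because sites collect what the schedule tells them to. Where they differ, either the data for the defined outcome are never collected, or sites differ in what they collect. An analysis plan cannot repair this later: a blood result not recorded or a questionnaire not completed is lost.

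For eGFR, the longer-term renal comparison is at stake. For EQ-5D-5L, it is the utilities behind a cost-effectiveness question that sits in the primary objective. Section 4.2 follows resource use and costs for at least 24 months and to the end of the trial, so utilities that stopped at month 12 would cover a shorter period than the costs. Records-only visits add a second route to missing utilities. The questionnaire asks participants to choose statements and to rate their health on the day, and clinical notes do not contain that.

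**Working it through.** The protocol states no figure to reproduce here. The check compares the scheduled time points and counts the gaps. The yearly measurements in section 4.2 are read as 24, 36 and 48 months.

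| Source | eGFR after baseline (months) | EQ-5D-5L after baseline (months) |
|---|---|---|
| Section 4.2 | 6, 12, 24, 36, 48 | 6, 12, 24, 36, 48 |
| Section 8.4.3 | 6 | not covered |
| Section 8.4.5 heading | not covered | 6, 12 |
| Table 2 | 6 | 6, 12, 24, 36, 48, 54 |

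**Step 1, eGFR.** Section 4.2 minus Table 2 leaves 12, 24, 36 and 48 months, so 0 of the 4 time points after month 6 are scheduled. By length of follow-up, the unscheduled share of the defined post-baseline values is:
- 24 months: 2 of 3 (12 and 24)
- 36 months: 3 of 4 (12, 24 and 36)
- 54 months: 4 of 5 (12, 24, 36 and 48)

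Section 8.4.3 and Table 2 agree with each other, and section 4.2 is the outlier. With one scheduled post-baseline value, the repeated-measures model in section 11.6 would have no renal course over time to estimate.

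**Step 2, EQ-5D-5L.** Section 4.2 minus Table 2 leaves nothing: Table 2 covers every defined time point and adds month 54. Section 4.2 minus the 8.4.5 heading leaves 24, 36 and 48 months. If a site followed the heading, the share of follow-up after the last utility would be (follow-up − 12) / follow-up:
- 24 months: 12/24 = 50%
- 36 months: 24/36 = 67%
- 54 months: 42/54 = 78%

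**Step 3, mode.** Section 8.5 allows telephone or records from month 12. Section 8.4.2 lists day 30 and months 12, 36, 48 and 54 for telephone or notes but leaves out month 24. Table 2 attaches its remote-visit footnote to the 36, 48 and 54 month columns, and the footnote text adds month 6. No section says that the participant must be contacted for the EQ-5D-5L when the rest of a visit comes from records. This step concerns EQ-5D-5L only, since a routine eGFR can be read from notes.

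**The case against.** The best defence concerns EQ-5D-5L. Section 4.2 and Table 2 agree up to month 48, sections 8.4.1 and 8.5 send sites to Table 2 for visit details, and only one sub-heading conflicts. Telephone contact is an allowed alternative to records, section 12.2.2 lists participant-reported questionnaires as a separate collection tool, and section 11.6.5 plans for missing data. All of this stands. A reader might infer that QALYs cannot be produced at all. The documents do not support that, because a site that follows Table 2 and contacts its participants will have the utilities.

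The defence does not remove the point. The ABPI heading just before 8.4.5 lists every visit to month 54, so a site could take the shorter EQ-5D-5L list as intended. Multiple imputation is mentioned only for the economic evaluation, and it is a poorer answer than a telephone call. For eGFR there is no comparable defence.

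A reader might also infer that having no EQ-5D-5L between baseline and month 6 biases QALYs towards surgery, and that a day-30 questionnaire is needed. That does not follow either. The protocol states no interpolation rule and gives no size or duration for an early loss of utility. It expects 43% of endovascular patients to need re-intervention within 3 years, and losses around those procedures could also fall between visits and act in the opposite direction. Day 30 is counted from randomisation, not from treatment, and may itself be done from notes.

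Nor do the documents show which participants would have records-only visits, so the direction of any resulting bias is unknown.

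**Conclusion.** The protocol contradicts itself on two secondary outcomes and leaves one collection rule unstated.

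- **eGFR:** the failure is unconditional. None of the 4 time points after month 6 is scheduled, so the outcome in section 4.2 cannot be produced from trial visits.
- **EQ-5D-5L timing:** the harm is conditional on sites following the 8.4.5 heading, in which case utilities are absent for 50% of a 24-month follow-up and 67% of a 36-month one. Under Table 2 this loss does not arise.
- **EQ-5D-5L mode:** the harm arises at each visit completed from records alone. How often that will happen is not stated, so its size cannot be given.

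The counts assume that yearly measurement after month 12 means 24, 36 and 48 months. The primary outcome, death or major amputation, is unaffected.

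**What to change.** 1. **eGFR.** Reconcile section 4.2 with section 8.4.3 and Table 2. Either define the outcome at month 6 only, which needs no extra blood tests but narrows the outcome, or state that later routine values are recorded from medical records, which adds data entry and will depend on what routine care has measured.
2. **EQ-5D-5L timing.** Correct the 8.4.5 heading to baseline, 6, 12, 24, 36, 48 and 54 months, as in Table 2, and align section 4.2 on whether month 54 is included. This is wording only.
3. **EQ-5D-5L mode.** State in section 8.5 and in the Table 2 footnote that the participant completes the EQ-5D-5L, by telephone or post, even when other data for the visit come from records. In the same edit, make sections 8.4.2 and 8.5 and the footnote agree on how month 24 may be conducted. The cost is a short contact at visits that would otherwise be done from notes.

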**Table 2. Schedule of Assessments**

| **VISIT** | **Time points** | | | | | | | | | |
| --- | --- | --- | --- | --- | --- | --- | --- | --- | --- | --- |
|  | **Baseline** | **Trial intervention** | **Day of Discharge** | **30 Days** | **6 months** | **12 months** | **24 months** | **36 months^1^** | **48 months^1^** | **54 months^1^** |
| **Visit window (days)**  (± number of days this visit can take place ahead or after its due date) | - | **-** | **-** | ± 7 days | ± 30days | ± 30 days | ± 30 days | ± 30 days | ± 30 days | ± 30 days |
| **Day** | 0 |  |  | 30 | 180 | 365 | 730 | 1095 | 1460 | 1643 |
| Eligibility check | x |  |  |  |  |  |  |  |  |  |
| Obtain informed consent | x |  |  |  |  |  |  |  |  |  |
| Randomisation (allocation of treatment) | x |  |  |  |  |  |  |  |  |  |
| Demographics | x |  |  |  |  |  |  |  |  |  |
| Medical history including cardiovascular risk factors | x |  |  |  | x |  |  |  |  |  |
| Details of anatomy (arteries) | x |  |  |  |  |  |  |  |  |  |
| Concomitant medications (statins and antithrombotics) | x |  | x | x | x | x | x | x | x | x |
| Review of clinical events |  |  | x | x | x | x | x | x | x | x |
| Days lost from regular activities |  |  |  |  | x | x | x | x | x | x |
| Estimated Glomerular Filtration Rate (eGFR) | x |  |  |  | x |  |  |  |  |  |
| Low Density Lipoprotein (LDL) value | x |  |  |  | x |  |  |  |  |  |
| Total Cholesterol value | x |  |  |  | x |  |  |  |  |  |
| HbA1C value | x |  |  |  | x |  |  |  |  |  |
| Ankle Brachial Pressure Index (ABPI) | x |  |  |  | x | x | x | x | x | x |
| EQ-5D-5L questionnaire | x |  |  |  | x | x | x | x | x | x |
| Details of intervention (type of surgery or endovascular treatment configuration and devices) |  | x |  |  |  |  |  |  |  |  |
| Admission to hospital or visit to primary care |  |  |  |  | x | x | x | x | x | x |
| Assessment of Adverse Events | x | x | x | x | x | x | x | x | x | x |

^1^ The follow up trial visitsmay be undertaken remotely either via telephone or through acquiring information through participant medical records. For 6 months, in the first instance please try to bring the patient in for a face-to-face appointment. If this is not possible then this follow-up visit may also be undertaken remotely via telephone or through acquiring information through participant medical records.

## Follow-up

The minimum follow up period for participants is 24 months after the time of randomisation. All follow up data will be collected from the date of randomisation. For month 6 follow-up, please make all efforts to ensure this takes place in person at the vascular clinic (as part of standard of NHS care appointments post-operatively). From month 12 onwards follow-up can be conducted via telephone or through collecting data from participant medical records. Please refer to **Table 2** for further details about follow up visits.

## Qualitative assessments

The Bristol QuinteT team will conduct interviews and qualitative assessments at each of the sites involved in the internal pilot. The QuinteT team will contact participants and healthcare professionals from the pilot sites to perform interviews assessing barriers and facilitators regarding participation in the trial. Formal qualitative assessments of participants or staff will not take place as part of the research during the main recruitment phase.

## Withdrawal of participation and consent criteria

Participants may withdraw their consent for the trial at any time if they choose not to continue, without prejudice for future care and they do not need to provide a reason why. However, if they are willing to provide a reason, it should be recorded on the relevant CRF. Participants will be asked to what extent they wish to withdraw their consent from the trial:

Prior to trial intervention, i.e., withdrawal from the trial intervention:

The participant would like to withdraw from their randomly allocated trial treatment i.e., they will not undergo the type of surgery as determined by randomisation, but will remain in trial follow-up and data will continue to be collected from them.

Post-trial intervention:

- Participant would like to withdraw from the attendance at clinic visits but gives permission for the trial related data to be collected from medical notes, NHS digital or contacted remotely (e.g., via telephone) to collect trial data
- Participant would like to withdraw from all trial assessments (both in person and remotely) but is happy for the study team to collect data from NHS databases in the future
- Participant would like to withdraw from the trial completely – no further data collection will be carried out

Withdrawal status will be documented on trial CRF and medical records. It is important to note that the data already collected prior to the point of withdrawal can still be analysed and included in the trial dataset.

## Assessment and management of risk

All clinical trials can be considered to involve an element of risk and in accordance to LCTU operating procedures, EVOCC has been assessed for any risks relating uniquely to this trial. Both surgical interventions are routinely used to treat this patient population therefore it has been concluded that the trial carries no higher risk than that of standard medical care.

## Pandemic adaptations

In the event of a pandemic (e.g., COVID-19) or local/national lockdowns which may affect EVOCC participants, sites should check ahead of scheduled trial visits that participants are able to attend in line with local Trust policy. Participants should follow government guidelines with regards to testing and self-isolation and MUST inform their Research Nurse/trial team if they are experiencing symptoms, have tested positive and/or must self-isolate. All scheduled trial visits can be rescheduled and certain data/assessments can be collected/performed remotely e.g. over the telephone or through medical notes.

Participant safety data will be collected during the course of the trial as usual.

In some cases, the data collection may be limited to primary endpoints, i.e., deaths and amputation data.

## End of trial

The end of the trial will occur when the final data capture takes place.

# SAFETY REPORTING

## Definitions

| **Term** | **Definition** |
| --- | --- |
| **Adverse Event (AE)** | Any untoward medical occurrence in a patient or clinical investigation participants, which does not necessarily have to have a causal relationship with this treatment.  An AE can therefore be any unfavourable and unintended sign (including an abnormal laboratory finding), symptom or disease temporally associated with the study, whether or not considered related to the study. |
| **Adverse Reaction (AR)** | An untoward and unintended response in a participant to an investigational medicinal product which is related to any dose administered to that participant.  The phrase "response to an investigational medicinal product" means that a causal relationship between a trial medication and an AE is at least a reasonable possibility, i.e. the relationship cannot be ruled out.  All cases judged by either the reporting medically qualified professional or the Sponsor as having a reasonable suspected causal relationship to the trial medication qualify as adverse reactions. It is important to note that this is entirely separate to the known side effects listed in the SmPC. It is specifically a temporal relationship between taking the drug, the half-life, and the time of the event or any valid alternative aetiology that would explain the event. |
| **Serious Adverse Event (SAE)** | A serious adverse event is any untoward medical occurrence that:   - results in death - is life-threatening - requires inpatient hospitalisation or prolongation of existing hospitalisation - results in persistent or significant disability/incapacity - consists of a congenital anomaly or birth defect   Other ‘important medical events’ may also be considered serious if they jeopardise the participant or require an intervention to prevent one of the above consequences.  NOTE: The term "life-threatening" in the definition of "serious" refers to an event in which the participant was at risk of death at the time of the event; it does not refer to an event which hypothetically might have caused death if it were more severe. |
| **Expected SERIOUS Adverse Events** | The following events are considered as expected SAEs. For the purposes of this trial such events do **NOT** require reporting to the EVOCC central team or Sponsor. These events should continue to be recorded in the medical records according to local practice and on the routine follow-up CRFs.   \| Bowel obstruction \| \| --- \| \| Acute kidney injury \| \| Arterial dissection \| \| Arterial pseudoaneurysm formation \| \| Atrial fibrillation (new) \| \| Bowel ischaemia \| \| Chest infection \| \| Diabetes (new diagnosis) \| \| Diabetic foot ulcer (new) \| \| Diabetic ketoacidosis \| \| Endovascular re-intervention (will have to be reported separately using the relevant form) \| \| Failure of endovascular closure device \| \| Fall \| \| Fasciotomy \| \| Haematoma (at site of surgery or percutaneous puncture) \| \| Heart failure (non-fatal) \| \| Hernia \| \| Hypertension (new diagnosis) \| \| Ileus \| \| Intermittent claudication (new diagnosis) \| \| Laparotomy \| \| Lower limb compartment syndrome \| \| Lower limb oedema \| \| Minor amputation (below the ankle joint) \| \| Myocardial infarction (non-fatal) \| \| Need for open surgical access to an artery during the index endovascular procedure \| \| Peripheral embolisation \| \| Peripheral embolisation, not requiring surgery or re-intervention \| \| Prescription of antibiotics for lower limb tissue loss (ulcer/gangrene) \| \| Re-admission to hospital within 30 days of randomisation \| \| Requirement for catheterisation (urinary catheter) \| \| Stent or graft occlusion \| \| Stent or graft thrombosis \| \| Stoma formation \| \| Stroke \| \| Surgical re-intervention (will have to be reported separately using the relevant form) \| \| Transient ischaemic attack \| \| Transient renal replacement therapy \| \| Urinary retention \| \| Urine infection \| \| Use of additional stent or additional endovascular device \| \| Venous thrombosis (deep and/or superficial) \| \| Viral infection \| \| Wound infection \| |

